# **Assessment of Safety**

## **Safety evaluation indicators**

1. Hematological tests: CBC
2. Biochemical serum tests: TP, AST, ALT, BUN, Cr, Na, K, FBS, CRP
3. Urinalysis: urine protein, urine sugar, occult blood, ketone body, urobilinogen, specific gravity, pH
4. Subjective findings (described in CTCAE v4.0-JCOG)

- General or systemic conditions at the time of administration
- Fever
- Skin and subcutaneous tissue disorder
- Gastrointestinal disorders: diarrhea, nausea, vomiting
- Metabolic and nutritional disorders: anorexia
- Nervous system disorders: somnolence

## **Assessment of Adverse Events**

For items (1) to (3) above (hematological tests, blood biochemical tests, and urinalysis), adverse events that fall under the following categories will be counted in CTCAEv4.0-JCOG.

- Grade 4 adverse events
- Grade 1/2/3 adverse events requiring hospitalization or prolonged hospitalization for treatment of the adverse event
- Grade 1/2/3 adverse events that are considered medically significant.

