## **Secondary Objectives**

- Efficacy
- Change in 10-meter walking time from Day 0 to Days 3 and 14.
- Change in measurements obtained with the Timed Up and Go Test from Day 0 to Day 3, 7, and 14.
- Degree of improvement in CSF cell count, protein, and neopterin concentration
- Safety
- Adverse events (nature and severity of adverse events, frequency of discontinuations and dropouts)

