## **Statistical Analysis Plan**

The significance level for the entire study is set at 10% on one side. p-values are valid to the fourth decimal place. Unless otherwise noted, categorical data will be summarized in terms of frequencies and proportions, and continuous data will be summarized in terms of basic statistics. Basic statistics will be calculated as mean, standard deviation, minimum and maximum values. No interim analysis will be performed. Missing data will not be supplemented, and rejected data will be excluded. Regarding the handling of abnormal data, no judgment will be made as to whether the data is abnormal or not, and all data will not be excluded.

If there are any changes from the original statistical analysis plan, the research protocol will be revised and the changes will be explained in the summary report of the clinical research.

Discontinuation cases and dropout cases will be excluded from the analysis. However, the results up to the time of hospital discharge will be used for cases of post-discharge dropout (e.g., those who were not able to return to Japan for a follow-up visit) where medication has been completed and no adverse events have been observed in the discharge examination.

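### Section 10.2 drops discontinuations and dropouts without exempting safety, and section 9.2 filters laboratory events below Grade 4, so the stated safety objective can be undercounted

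*Protocol*

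**What the plan says.** **Objective.** Section 3.2 (Secondary Objectives) gives the safety objective as "Adverse events (nature and severity of adverse events, frequency of discontinuations and dropouts".

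**Who is analysed.** Section 10.2 (Statistical Analysis Plan) takes patients who discontinue or drop out out of the analysis. It does not limit this to efficacy, and it names no separate set for safety. The one exception concerns patients lost after discharge: their results up to discharge are used "where medication has been completed and no adverse events have been observed in the discharge examination".

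**What leads to stopping.** Section 6.4 (Dosing Guidelines) has medication discontinued for markedly abnormal blood results, for worsening of the primary disease, and for impairment due to acidemia.

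**What is counted.** Section 9.2 (Assessment of Adverse Events) says of the blood count, biochemistry and urine tests that "adverse events that fall under the following categories will be counted in CTCAEv4.0-JCOG". There are three categories. The first takes every event of Grade 4, without further condition. The second covers lower grades that affect the hospital stay: "Grade 1/2/3 adverse events requiring hospitalization or prolonged hospitalization for treatment of the adverse event". The third, for which no criterion is given, is "Grade 1/2/3 adverse events that are considered medically significant".

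The fourth group of indicators in section 9.1 is listed as "Subjective findings (described in CTCAE v4.0-JCOG") and covers fever, skin, gastrointestinal, appetite and somnolence findings. The section 9.2 categories do not apply to it.

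**The concern.** Two stated rules act on the same secondary objective.

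The first decides which patients contribute. Stopping for toxicity is an outcome of interest, yet under section 10.2 it is also a reason to leave the analysis. The single exception is itself conditioned on a safety finding. A discontinuation frequency cannot be estimated in a set from which discontinuations have been taken out.

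The second decides which laboratory events contribute. The section 9.2 list resembles a filter for serious events used as the counting rule. An asymptomatic Grade 3 change in a liver enzyme or in potassium is counted only if someone considers it medically significant, and the protocol gives no criterion for that.

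Section 10.1 justifies the sample size by calling the trial a pilot to confirm safety and efficacy. With 20 patients, one or two patients or events decide what the safety summary shows.

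**Working it through.** The protocol gives no adverse event rate and no precision target, so there is no figure of its own to reproduce. The rules are traced first, then illustrated. The only documented number is N = 20 (section 10.1). All event counts below are assumptions, and all 20 patients are taken to have been dosed.

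**1. Tracing section 10.2, read literally**

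| Patient | In the analysis? |
|---|---|
| Stops medication for a marked blood abnormality (section 6.4), if that makes a discontinuation case | No |
| Leaves before discharge or before finishing medication, with or without an adverse event | No |
| Finishes medication, lost after discharge, adverse event seen at the discharge examination | No |
| Finishes medication, lost after discharge, none seen at that examination | Yes, up to discharge |
| Completes the study | Yes |

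Only the fourth row keeps a discontinuation or dropout. In the analysed set the frequency named in section 3.2 is therefore zero apart from those patients.

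**2. Effect on the proportion with an adverse event**

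Let x of n patients have an event. Remove m patients, d of them with an event. The reported proportion is (x − d)/(n − m). It falls below x/n when d/m is greater than x/n, that is, when events are commoner among those removed than overall. The section 6.4 stopping reasons and the discharge condition both favour that.

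If every removed patient had an event (d = m), with exact (Clopper-Pearson) 95% intervals:

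| Assumed x of 20 | Removed | Reported |
|---|---|---|
| 2 | 0 | 2/20 = 10.0% (1.2 to 31.7) |
| 2 | 1 | 1/19 = 5.3% (0.1 to 26.0) |
| 2 | 2 | 0/18 = 0% (0 to 18.5) |
| 4 | 0 | 4/20 = 20.0% (5.7 to 43.7) |
| 4 | 1 | 3/19 = 15.8% (3.4 to 39.6) |
| 4 | 2 | 2/18 = 11.1% (1.4 to 34.7) |
| 4 | 4 | 0/16 = 0% (0 to 20.6) |

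The opposite case is possible. If x = 2 and the two patients removed had no event, the result is 2/18 = 11.1%, slightly above 10%. The number of affected patients can only fall; the proportion falls when removal is linked to toxicity.

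**3. Effect of the section 9.2 filter**

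Assume 10 of 20 patients have a Grade 1 to 3 laboratory or urine event, and let f be the share of them that meets one of the two conditions. The counted rate is 10f/20.

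| f | 0 | 0.10 | 0.25 | 0.50 | 1 |
|---|---|---|---|---|---|
| Counted rate | 0% | 5% | 12.5% | 25% | 50% |

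The protocol does not fix f. The loss can be anything from none to all of these events.

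**The case against.** **Section 10.2 may be meant for efficacy only.** It opens with the significance level and p-values, and a discontinuation frequency makes sense only over enrolled patients. This is plausible. But the text does not say so, and an exception that depends on adverse events makes an efficacy-only reading harder to assume. What stands is that the defect may be one of wording.

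**The data are kept.** Section 9.3 has the safety indicators recorded on Days 0, 7, 14 and 28 and all safety information entered in the medical record. Section 10.2 also gives minimum and maximum for continuous data, so extreme laboratory values of analysed patients would still show. Both points are right, and they make the problem repairable. Recording an event, however, is not the same as counting it. Section 4.4 promises analysis of the data after discontinuation, but it concerns stopping the whole study.

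**Safety tables and analysis sets are commonly left to a separate plan.** That is true of layout. The point here rests on two rules that the protocol does state.

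A reader might also infer more than the text supports:

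- *Patients who leave with an adverse event vanish while those without one stay.* Patients without an event who leave before discharge or before finishing medication are excluded too. An event that resolved before the discharge examination does not, on the wording, block retention.
- *No severity distribution can be reported.* The filter covers laboratory and urine tests only; symptomatic findings are outside it.
- *The hospitalization condition is empty for inpatients.* The criterion includes prolonged stay, and new admission is possible between discharge (Day 14) and the last visit (Day 28).
- *An unblinded investigator decides what is significant.* The protocol does not say who judges.

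**Conclusion.** The concern holds as a conflict between the safety objective and two stated rules. Taken literally, section 10.2 removes patients partly because of toxicity and brings the discontinuation and dropout frequency close to zero in the analysed set, the exception being the retained post-discharge dropouts. Section 9.2 can undercount laboratory and urine events below Grade 4 by an amount that depends on an undefined judgment.

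The size cannot be fixed from the protocol. Under assumed counts, 10% becomes 5.3% or 0% when one or both of two affected patients are removed, and a 50% rate of Grade 1 to 3 laboratory events could be counted anywhere from 0% to 50%. The zero results are worst cases. The first needs every affected patient to be removed; the second needs every such event to be judged not significant and none to need or prolong hospitalization. The first result also assumes that stopping medication under section 6.4 makes a patient a discontinuation case, which the protocol does not define.

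A reader might conclude that the trial cannot assess safety at all. The documents do not support that: safety is a secondary objective, symptomatic findings are not filtered by section 9.2, and the underlying data are recorded. This should be fixed; it does not invalidate the design.

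**What to change.** **Section 10.2**

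- State that the exclusion of discontinuations and dropouts applies to efficacy only.
- Analyse safety in all patients who took at least one dose, with no removal for discontinuation, dropout or adverse events.
- Report discontinuations and dropouts, with reasons, over all enrolled patients.

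**Section 9.2**

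- Tabulate laboratory and urine abnormalities by worst CTCAE grade per patient.
- Keep the present three categories as a separate subset of serious or significant events.

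**Cost.** A protocol revision, explained in the summary report as section 10.2 already requires for changes to the analysis plan, and a few more table rows. No new measurements are needed: section 8.2 schedules the blood and urine tests and section 9.3 has the results recorded. The safety profile may look less favourable than under the present rules.

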## **Recording Adverse Events**

The evaluation of safety assessment indicators in above will be conducted on Day 0, Day 7, Day 14, and Day 28, and recorded in the medical record and case report form. If the sub-investigator obtains safety information, he or she will record all safety information in the medical record and analyze the safety issues with the principal investigator. In the case of a serious event, a report on safety information will be submitted to the Kagoshima University Clinical Research Review Committee and the Director of the Kagoshima University Hospital.

## **Treatment and Follow-Up of Adverse Events**

Observation period of the subject of the clinical research after the occurrence of the disease, etc. Necessary examination and treatment will be taken as appropriate. If there is no improvement at the end of the study (21 days after the end of dosing; Day 28), evaluation and treatment will be continued until complete remission after the end of the study.

# **Statistics**

## **Data analysis**

Statistical analyst:

[name], Associate Professor, Department of Neurology

Target number of targets and rationale for setting them:

Number of cases; 20 cases

Rationale for setting:

A pilot study (safety and efficacy confirmation study).

## **Statistical Analysis Plan**

The significance level for the entire study is set at 10% on one side. p-values are valid to the fourth decimal place. Unless otherwise noted, categorical data will be summarized in terms of frequencies and proportions, and continuous data will be summarized in terms of basic statistics. Basic statistics will be calculated as mean, standard deviation, minimum and maximum values. No interim analysis will be performed. Missing data will not be supplemented, and rejected data will be excluded. Regarding the handling of abnormal data, no judgment will be made as to whether the data is abnormal or not, and all data will not be excluded.

If there are any changes from the original statistical analysis plan, the research protocol will be revised and the changes will be explained in the summary report of the clinical research.

Discontinuation cases and dropout cases will be excluded from the analysis. However, the results up to the time of hospital discharge will be used for cases of post-discharge dropout (e.g., those who were not able to return to Japan for a follow-up visit) where medication has been completed and no adverse events have been observed in the discharge examination.

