## **Inclusion Criteria**

Subjects eligible for enrollment in the study must meet all of the following criteria:

1. Patient with HAM/TSP
2. Age ≥ 20 years at the time of consent
3. Ongoing medication for HAM/TSP, with no changes in 12 weeks before enrollment. Subjects on maintenance therapy with steroids must have been receiving ≤ 10 mg/day prednisolone equivalent continuously for at least 12 weeks before enrollment.
4. Subjects are able to walk ≥ 10 meters at screening (use of a single cane, double canes or any walking aid is allowed)
5. Voluntary written informed consent to participate in the study
6. Subjects are able to see the Kagoshima University Hospital on the schedule days

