## **Primary and Secondary Endpoints**

The primary endpoint:

- Change in 10-meter walking time from Day0 to Day7

The secondary endpoints:

- Efficacy
- Change in 10m walking time between Day 0 and Days 3 and 14
- Change in measurements obtained with the Timed Up and Go from Day 0 to Day 3, 7, and 14
- Degree of improvement in CSF cell count, protein, and neopterin concentration

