Mark the beginning and end of a 10 m straight line on the floor with tape, etc., and measure the time required for walking with a stopwatch.

If a walking aid (one-handed cane, two-handed cane, etc.) is used for walking, it will be measured without changing the aid during the study period.

The test will be conducted after a short stretching session before the walking test. (The content of stretching will be decided for each patient.)

Start walking 2 m before the starting point, and measure the time taken from the time when the patient passes the starting point to the time when the patient passes the ending point.

1. Time Up and Go Test (Day -28, 0, 3, 7, 14, 28)

＜Implementation Method＞

The starting position is leaning back lightly, with hands on thighs.

The starting posture is to lean back lightly on the backrest and place the hands on the thighs. In this case, both feet should be on the floor.

The time taken to stand up from the armchair, walk around the marker 3m away, and sit down on the chair again shall be measured. 0m point shall be the front leg of the chair, and 3m point shall be the center of the cone.

The subject is asked to perform a series of movements at "normal walking speed" and "maximum walking speed" (two times in total) following the call of the measurer.

The measurer measures the time from the time when a part of the subject's body starts to move to the time when the buttocks touch the ground. (This is not a strict rule; it should be from standing to sitting.)

After two measurements, the smaller value (faster time) shall be adopted, and the number of seconds to one decimal place shall be recorded. (The second digit shall be rounded off.)

[Precautions for measurement]

If a walking aid is used in daily life, it should be used as it is. If you use a walking aid in your daily life, use it as it is.

The way the subject turns the cone is up to the subject.

When the subject goes around the cone, there is a high risk of falling, and when the subject sits down, there is a risk of falling due to excessive momentum, so the measurer should be careful. (Be especially careful on tatami mats, as they are slippery.)

1. OMDS (Day -28, 0, 3, 7, 14, 28)

<Implementation methods>

The patient’s condition will be determined according to the table below and scored.

| Grade | Motor Disability Grade |
| --- | --- |
| 0 | Normal gait and running |
| 1 | Normal gait but runs slowly |
| 2 | Abnormal gait (staggering or spastic) |

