| 3 | Unable to run |
| 4 | Need handrail to climb stairs |
| 5 | Needs a cane (unilateral support) to walk |
| 6 | Needs bilateral support to walk |
| 7 | Can walk 5-10m with bilateral support |
| 8 | Can walk 1-5m with bilateral support |
| 9 | Cannot walk, but able to crawl |
| 10 | Cannot crawl, but able to move using arms |
| 11 | Cannot move around, but able to turn over in bed |
| 12 | Cannot turn over in bed |
| 13 | Cannot even move toes |

1. Modified Ashworth Scale (Day -28, 0, 3, 7, 14, 28)

The patient’s condition will be determined according to the table below and scored.

| Grade | Description |
| --- | --- |
| 0 | No increase muscle tone |
| 1 | Slight increase in muscle tone, manifested by a catch and release or by minimal resistance at the end of motion when the affected part(s) in moved in flexion or extension |
| 1+ | Slight increase in muscle tone, manifested by a catch, followed by minimal resistance throughout the remainder (less than half) of the ROM |
| 2 | More marked increase in muscle tone through most of the ROM, but affected part(s) easily moved |
| 3 | Considerable increase in muscle tone, passive movement difficult |
| 4 | Affected part(s) rigid in flexion or extension |

1. OABSS (Day -28, 0, 3, 7, 14, 28)

The following questionnaire will be used to survey the period from the date of the last response to today.

| Question | Frequency | Score |
| --- | --- | --- |
| Q1. How many times do you typically urinate from walking in the morning to going to sleep at night? | 7 or less | 0 |
|  | 8-14 | 1 |
|  | 15 or more | 2 |
| Q2. How many times do you typically wake up to urinate at night? | None | 0 |
|  | 1 | 1 |
|  | 2 | 2 |
|  | 3 or more | 3 |
| Q3. How often do you have a sudden desire to urinate that is difficult to defer? | None | 0 |
|  | Less than once a week | 1 |
|  | Once a week or more | 2 |
|  | About once a day | 3 |
|  | 2-4 times a day | 4 |
|  | 5 times a day or more | 5 |
| Q4. How often do you leak urine because you cannot defer the sudden desire to urinate? | None | 0 |
|  | Less than once a week | 1 |
|  | Once a week or more | 2 |
|  | About once a day | 3 |
|  | 2-4 times a day | 4 |
|  | 5 times a day or more | 5 |

1. Assessment of pain and numbness using VAS (Day -28, 0, 3, 7, 14, 28)

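### A patient who cannot complete the 10-meter walk at Day 7 has no primary score, and both exclusion rules in section 10.2 then remove that patient from the Day 7 mean change

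*Protocol*

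**What the plan says.** All references are to the protocol.

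- **Endpoint.** Section 8.1 defines the primary endpoint as "Change in 10-meter walking time from Day0 to Day7".
- **How the score arises.** Section 8.2 tells the assessor to "measure the time taken from the time when the patient passes the starting point to the time when the patient passes the ending point". Any walking aid stays the same: "it will be measured without changing the aid during the study period". No ceiling time, rank or code is given for a walk that is not completed.
- **Missing values.** Section 10.2: "Missing data will not be supplemented, and rejected data will be excluded".
- **Discontinuations.** Section 10.2 also leaves discontinued and dropped-out patients out of the analysis. The one exception covers patients lost after discharge who had finished the drug without adverse events at the discharge examination.
- **Worsening.** Section 6.2 stops the study when symptoms worsen significantly. Section 6.4 stops the medication when symptoms of the primary disease worsen.
- **Test setting.** Section 10.1 plans 20 patients, section 5.1 has no control group, and section 10.2 sets a one-sided 10% level and summarises continuous data by mean, SD, minimum and maximum.

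**The concern.** A patient who improves or stays stable can produce a Day 7 time. A patient who loses the ability to walk 10 m cannot. The value is then absent because the outcome is bad, and the rules of 10.2 leave that patient out of the Day 7 change. The protocol's own disability scale contains this state: OMDS grade 7 reads "Can walk 5-10m with bilateral support".

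The error runs in one direction, toward apparent benefit. No control arm loses patients in the same way to offset it. With 20 patients and a one-sided 10% level, one or two such losses could decide whether the trial reports an improvement.

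**Working it through.** **Step 1: follow the patient through the rules.**

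| Situation at Day 7 | Rule that applies | Result for the Day 7 change |
|---|---|---|
| Walk completed, however slowly | Section 10.2 keeps extreme recorded values | Included |
| Still on study, walk not completed (for example, inability first seen at Day 7) | Section 10.2, missing-data sentence | Lost |
| Worsened earlier and stopped under 6.2 or 6.4 | Section 10.2, discontinuation sentence | Lost |

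The second row is a real possibility. Section 9.4 places Day 28 at 21 days after the end of dosing, so dosing ends at Day 28 − 21 = Day 7. A patient first found unable at the Day 7 test is at the end of treatment, so stopping the drug is no longer what removes that patient. The exception for patients lost after discharge does not help in either lost row, because it keeps recorded results and cannot supply a time that was never obtained.

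**Step 2: inputs for the size.** From the protocol: n = 20, one group, one-sided level 0.10. Assumed, because the protocol gives none of them: no true effect, normally distributed changes in SD units (positive = slower), a one-sample t test on the available changes, and the number of patients lost. The planned sample size cannot be reproduced, since 10.1 gives only the pilot purpose as its rationale.

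**Step 3: shift of the mean.** The expected largest of 20 standard normal values is about 1.87 and the second largest about 1.41. The average over all 20 is 0.

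- Worst one lost: −1.87 / 19 = −0.10 SD.
- Worst two lost: −(1.87 + 1.41) / 18 = −0.18 SD.

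**Step 4: false-positive rate, worst k patients lost in every trial.** This comes from simulation. The t test uses the remaining 20 − k patients. The comparison is an exact signed-rank test on all 20, with the k patients placed at the worst ranks.

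| k lost | t test on those left | Signed-rank, worst rank |
|---|---|---|
| 0 | 0.10 | 0.10 |
| 1 | 0.22 | 0.08 |
| 2 | 0.36 | 0.06 |

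**Step 5: false-positive rate when loss depends on a threshold.** Here only changes beyond a cut-off are unscorable, so many trials lose nobody. The expected number lost is 20 × P(Z > cut-off).

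| Unscorable if slowing exceeds | Expected number of 20 | t test on those left |
|---|---|---|
| 3.0 SD | 0.03 | 0.10 |
| 2.5 SD | 0.12 | 0.11 |
| 2.0 SD | 0.5 | 0.14 |
| 1.5 SD | 1.3 | 0.25 |

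**Step 6: a low assumed risk.** Suppose each patient has a 1% chance of being unable, and those unable are the worst changes. The chances of 0, 1 and 2 losses in 20 are 0.818, 0.165 and 0.016. The overall rate is about 0.818 × 0.10 + 0.165 × 0.22 + 0.016 × 0.36 = 0.12.

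**The case against.** The strongest case against is that the event may be rare. The interval is seven days. Patients must have had unchanged medication for 12 weeks and a screening walking time within 30% of recent values, and rehabilitation is held constant. No rate is stated, and Steps 5 and 6 show the inflation falling to almost nothing when inability is uncommon. This stands, and it limits the size of the point. It does not remove the gap in the rules.

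A second objection is that scoring of inability may be left to a separate SAP. Section 10.2 itself fixes the missing-data and discontinuation rules and requires a protocol revision for any change, so the point can be judged here.

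A reader might also infer several stronger things that the protocol does not support:

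- *That the missing-data sentence is the only rule at work, so retaining discontinued patients would not help.* Sections 6.2 and 6.4 would make many worsened patients discontinuation cases. A repair must reach both sentences.
- *That inclusion 4 admits patients who cannot do the test.* It asks that "Subjects are able to walk ≥ 10 meters at screening", while the test says "Start walking 2 m before the starting point" and so needs 12 m. But section 8.2 schedules the test at screening, and exclusion 2 needs a screening time for comparison. Rewording inclusion 4 would change almost nothing.
- *That a patient who comes to need a different aid has no time.* A slower walk with the original aid still yields a time, and extreme times are kept.
- *That the same argument covers the Timed Up and Go.* That test runs 3 m out and back, and the fixed-aid wording stands under the 10-meter walk only.
- *That the patient is deleted altogether.* On the missing-value route, only the Day 7 change is lost; other visits and endpoints remain.

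**Conclusion.** The point holds. The protocol gives no score to an uncompleted walk, and two separate sentences of section 10.2 remove the patients concerned. The resulting bias in the Day 7 mean change favours the drug.

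Its size is conditional. A false-positive rate of about 22% or 36% applies if exactly the worst one or two of 20 patients are lost. It is 10% to 14% if slowing beyond 3.0 to 2.0 SD is unscorable. All these figures assume no drug effect, normal changes and a t test that the protocol does not name. A reader might take 22% or 36% as the trial's expected error rate. The documents do not support that, because they give no frequency of inability. The point should be corrected, but it does not show that the trial's result will be wrong.

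**What to change.** In section 10.2, amend both the missing-data sentence and the discontinuation sentence, for example:

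*A patient who cannot complete the 10-meter walk at a scheduled visit because of inability, including a patient who discontinued because of worsening, is recorded as unable, kept in the analysis and given the worst rank of change. The primary endpoint is tested with a one-sided signed-rank test on these ranks. The mean change among completers is reported beside it, with the number unable.*

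If several patients are unable, their order among themselves does not matter, because all carry the top ranks with the same sign. By Step 4, the false-positive rate then stays within the stated 10%.

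The cost is a short amendment to 10.2 and an entry for inability on the case report form. The statistical downside is a slight loss of efficiency if changes are normal and nobody is unable. No change is needed to inclusion 4 or to the Timed Up and Go, and the fix touches no dosing or stopping rule.
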